**IRB Protocol Template**

**Title:** **Patient participation in decision making with medication adherence in osteoporosis**

**Protocol Version/Date:**  **02-16-2010**

**IRB#:08-006070**

**PI: [name] MSc**

**Abstract:**

Bisphosphonates can reduce fracture risk in patients with osteoporosis. Patients may not start and adhere to bisphosphonates, consequently losing quality and length of life. We hypothesize that a decision aid that improves patient-provider communication about fracture risk will improve the quality of treatment decisions: patients will become more involved in the decision-making process and decisions will be more consistent with patients' values and health care goals. We expect this will lead to increased bisphosphonate start and adherence in patients at increased risk of fracture, and that patient with a low risk of fracture will stop or not start bisphosphonates.

To test our hypothesis, we developed OSTEOPOROSIS CHOICE, a decision aid to support the decision to use (or not use) bisphosphonates in postmenopausal women at risk for osteoporotic fractures, based on individualized fracture risk estimates. This practical randomized trial will test the decision aid + risk calculation vs. consultations with only the fracture risk calculator vs. consultations with usual care (no risk calculation, no decision aid). We hypothesize that risk estimation is insufficient to improve quality of decision making and adherence, and both can be enhanced with the full decision aid.

The Normalization Process Analysis (addendum) will enable us to understand the conditions that are necessary to support the implementation / normalization of this decision aid in clinical practice.

The Normalization Process Theory (NPT), developed by [name], can inform the evaluation of the processes by which complex interventions, such as decision aids, can become embedded in health care practice. Using this model in the OSTEOPOROSIS CHOICE II study, will enable us to understand the conditions that are necessary to support the implementation / normalization of this decision aid into routine practice. We will focus on the role of the nurse in the outpatient setting, who typically sees the patient prior to the appointment with their primary clinician.

We will also analyze a subset of patient-clinician encounters to identify organizational, patient, and provider characteristics that promote or inhibit uptake of the decision aid in clinical practice.

**Schematic Design of the Study:**

We are conducting a randomized controlled trial (RCT) of a decision aid for female patients with osteopenia or osteoporosis. Patients will be randomized to one of three arms: Intervention (decision aid + FRAX calculator*), FRAX calculator, or Usual care (no FRAX calculation and no decision aid). Clinicians who consent to participate will administer the decision aid to those patients randomized to the intervention.

The Normalization Process Analysis, addendum to Osteoporosis Choice II protocol, is a qualitative assessment.

**The FRAX (Fracture Risk Assessment) tool developed by the World Health Organization is available at: http://www.shef.ac.uk/FRAX/*

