**Patient Population:**

**Number (total, each subgroup)** 150, 50,50, and 50

We expect that 30 patients will take part at Olmsted Medical Center, Rochester

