**Inclusion Criteria:**

- 1. Peri/ post menopausal Caucasian, Black, Hispanic and Asian women aged 50-90 with a T-score < -1.0.
  2. Identified by their providers as potentially eligible for treatment with a bisphosphonate.
  3. Are available for phone follow-up 6 months after randomization.
  4. Patients with FRAX <20% risk who have taken a bisphosphonate for < 5 years.

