**Exclusion Criteria:**

1) Patients with FRAX >20% risk who are taking bisphosphonates.

2) Have major learning barriers (in their provider's judgment), such as hearing impairment, or dementia, that would compromise their ability to give written informed consent

3) Are non-English speaking

**Step-by-Step Schedule (include all procedures, therapies – attach a table or flow chart if there are multiple procedures or visits and indicate the window of number of days in which the participant may return for follow-up visits):**

See attachment (Protocol Steps - Trial Flowsheet)

**Biospecimen (types, number, volume, processing, storage):** Not applicable

**Plan for Dose Modification if Toxicity occurs (if applicable):** Not applicable

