**Power Statement:**

We plan to enroll and randomize 150 eligible patients. While this number of patients is insufficient to reach a definitive answer about the efficacy of our decision aid and its' effects on adherence, it is sufficient to ascertain meaningful differences in tool acceptability and knowledge gains as well as inform a plausible effect size in relation to its impact on adherence. Thus, we will be powered (80%) to detect a difference (alpha = 0.05) in adherence rates at 6 months of 30%. While a minimally important increase in adherence has not been reported, a 10% increase (e.g. from 65% to 75%) appears as the smallest difference that could justify the use of decision aids in practice. We will pool patients from the first pilot (with the exception of the low risk patients on bisphosphonates at time of recruitment), which will generate 95% confidence intervals with a precision of 17%, or a 90% confidence interval (akin to a one-sided hypothesis test) of 14% (44). This means that we have enough power to abandon plans for a multicenter trial when the point estimate of our trial indicates a decrease in adherence because of the use of the decision aid of greater than or equal to 7% or greater than or equal to 4% respectively.

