**Data Analysis:**

We will use hierarchical models (that take into account clustering/contamination) to estimate the absolute difference in bisphosphonates initiation and adherence rates between groups and the associated 95% confidence interval. We will use similar analyses for other dichotomous outcomes (e.g., adherence). We will use generalized estimation equations to compare the change in intermediate continuous outcomes (decisional conflict, knowledge) by arm after adjusting for clustering across physicians. With the exception of the low risk group on treatment, an analysis of Osteo II data may be combined with the Osteo I Choice study.

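### Stratifying allocation by current bisphosphonate use, or adjusting for it, would give the Osteo II use and adherence comparison a small, almost free gain in precision

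*Protocol*

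**What the plan says.** All references are to the Protocol.

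- **Allocation.** Schematic Design of the Study: "Patients will be randomized to one of three arms". No stratification factor is named. Patient Population gives the numbers as "150, 50,50, and 50".
- **Who enters.** The Inclusion Criteria admit "Patients with FRAX <20% risk who have taken a bisphosphonate for < 5 years". The Exclusion Criteria remove "Patients with FRAX >20% risk who are taking bisphosphonates". Apart from a FRAX of exactly 20%, which neither criterion covers, enrolled current users are therefore the low-risk women on treatment.
- **Outcome.** Under Endpoints, starting or stopping medication is one of three primary outcomes, assessed at the clinician visit and at 6 months.
- **Power.** Power Statement: "we will be powered (80%) to detect a difference (alpha = 0.05) in adherence rates at 6 months of 30" percentage points. It adds that "a 10% increase (e.g. from 65% to 75%) appears as the smallest difference" that could justify using the aid.
- **Models.** Data Analysis plans "hierarchical models (that take into account clustering/contamination) to estimate the absolute difference in bisphosphonates initiation and adherence rates between groups". Baseline use is not mentioned.
- **Pooling.** Data Analysis: "With the exception of the low risk group on treatment, an analysis of Osteo II data may be combined" with the earlier study. The Power Statement makes the same exclusion.

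**The concern.** The Protocol itself treats low-risk women on treatment as a separate kind of patient. It expects the aid to lead low-risk women to stop or not start and high-risk women to start and adhere, and it removes the treated low-risk group before pooling. One yes/no item, already needed for eligibility, identifies the group. It is also likely to be among the strongest predictors of whether a woman is taking a bisphosphonate at 6 months.

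With 50 women per arm, the share of current users can differ between arms by chance. In any Osteo II model that puts both groups together, that difference passes into the estimated effect on use or adherence unless the design balances it or the model adjusts for it. The stop comparison may also rest on uneven, small numbers per arm. What is at stake is precision in an already small trial, and a crude estimate that is hard to read once an imbalance has been seen.

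**Working it through.** **1. The plan's own figures.** The Power Statement gives 80% power, alpha 0.05 (two-sided assumed) and a 30-point difference, but no base rates. For 35% versus 65%:

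n = [1.96 × √(2 × 0.5 × 0.5) + 0.842 × √(0.35 × 0.65 + 0.65 × 0.35)]² / 0.30² = 42.4, so 43 per arm; 49 with continuity correction.

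40% versus 70% also gives 49. The stated 50 per arm is thus reproduced at mid-range rates with every woman counted. At 65% versus 95% only 34 would be needed. Nothing in the statement restricts it to users or non-users, so I read it as covering both groups together.

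The abandonment thresholds also reproduce from the pooled precision and the 10-point smallest worthwhile difference: 17 − 10 = 7 and 14 − 10 = 4.

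**2. Assumptions.** The Protocol gives neither s, the share of current users at entry, nor D, the gap in 6-month use or adherence between users and non-users. I take s = 25% (range 15-50%) and D = 40 points (range 20-60). The central case is 80% use in current users and 40% in the others.

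**3. Imbalance in the share.** With 150 women in three equal arms, the SD of the number of users in one arm is

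√(50 × s(1 − s) × 100/149) = √(50 × 0.1875 × 0.671) = 2.51 at s = 0.25.

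The expected number is 12.5, with a 95% range of 12.5 ± 1.96 × 2.51, about 7.6 to 17.4. The SD of the difference in share between two arms is √3 × 2.51/50 = 8.7 points. The approximation √(2s(1 − s)/50) gives the same value.

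**4. Effect on the crude difference.** The shift is D times the difference in share.

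| s | D (points) | SD of shift (points) | 95% range (points) |
|---|---|---|---|
| 15% | 20 | 1.4 | ±2.8 |
| 20% | 20 | 1.6 | ±3.1 |
| 15% | 40 | 2.9 | ±5.6 |
| 25% | 40 | 3.5 | ±6.8 |
| 30% | 40 | 3.7 | ±7.2 |
| 40% | 40 | 3.9 | ±7.7 |
| 50% | 40 | 4.0 | ±7.8 |
| 50% | 60 | 6.0 | ±11.8 |

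**5. Gain from adjusting.** The share of outcome variance explained is R² = s(1 − s)D² / [p(1 − p)], with p the overall rate. The SE ratio is √(1 − R²). With 80% versus 40% use:

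- s = 15%: p = 0.46, R² = 0.0204/0.2484 = 0.08, SE 4% smaller.
- s = 25%: p = 0.50, R² = 0.0300/0.2500 = 0.12, SE 6% smaller.
- s = 40%: p = 0.56, R² = 0.0384/0.2464 = 0.16, SE 8% smaller.

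In sample-size terms, 150/(1 − R²) − 150 is about 13 to 28 women. At an overall rate of 65%, the 95% half-width falls from 18.7 to 17.3 points for s = 30% and D = 40.

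**6. The pooled analysis.** Low-risk users are removed there and high-risk users were never eligible, so s is about 0 and the shift is about 0. What remains is uneven arm size. Even 32 versus 43 women, instead of 37.5 each, changes the SE by √[(1/32 + 1/43)/(2/37.5)] = 1.01, about 1%.

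**The case against.** **Silence is not a statement.** The allocation sentence is compatible with stratified randomisation, the trial flowsheet is attached but not shown, and a statistical analysis plan may list covariates. This stands: the Protocol never says that allocation is unstratified or that clustering is the only adjustment. It weakens the covariate half more than the allocation half. Stratification is a design feature that must be fixed before the first patient, and the design section is where it belongs.

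**Chance imbalance is not bias.** This also stands. The imbalance is part of the sampling error that an unadjusted 95% interval covers on average. Adjustment narrows the interval and removes the shift once an imbalance has been observed; it does not repair an invalid analysis.

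**The outcome may not be mixed.** A current user cannot initiate, so an initiation model would naturally hold non-users only. If starting and stopping are each analysed in their own group, the covariate drops out and stratification only evens the numbers. About 12 users per arm says little even when balanced. The gain therefore applies to 6-month use or adherence models that combine the groups, as the power statement appears to do.

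**A stronger reading to resist.** A reader might set shifts of 4 to 7 points beside the 7- and 4-point abandonment thresholds and infer that chance imbalance could trip them. The documents do not support this. The thresholds come from the precision of the pooled analysis, which leaves out current users. The Power Statement's reference to the trial's own point estimate is loose, but it follows directly on the pooled precision figures.

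**Conclusion.** The point holds as an optional improvement, not as an error in the plan. In the Osteo II analysis, a predictor known at entry, which the Protocol itself uses to separate patients, is not named as a stratification factor or a covariate.

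Under 15-50% current users and a 20-60 point gap, imbalance contributes an SD of about 1.4 to 6 points to the unadjusted difference. The central case is 3.5 points, roughly a third of the 10-point smallest worthwhile difference. At a 40-point gap with 15-40% users, the SE falls by about 4-8%. All of this rests on assumed shares and gaps; at 20% users and a 20-point gap the SD is only 1.6 points. The abandonment decision is unaffected.

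**What to change.** - **Schematic Design of the Study:** state that allocation is 1:1:1 within current bisphosphonate use at entry (yes/no). If the flowsheet already provides for this, say so here.
- **Data Analysis:** include current use as a fixed covariate in every Osteo II model of bisphosphonate use or adherence that combines users and non-users. Obtain the absolute difference by standardising over current use, so that it stays on the risk-difference scale the Protocol asks for.
- **If enrolment has begun:** keep the existing allocation and apply the covariate alone.
- **Pooled analysis:** no change is needed on this account.

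The cost is one more item to confirm before allocation, one extra allocation list and one model term. The item is already collected for eligibility.

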**Aims:**

Bisphosphonates can reduce fracture risk in patients with osteoporosis. However, many patients may not start and adhere to bisphosphonates, consequently losing independence, quality, and length of life. Women who are at a low risk for developing an osteoporotic fracture may be unaware of their minimal risk and side effects of treatment, and may be receiving treatment without knowledge of their low risk. We hypothesize that a decision aid that efficiently improves patient education and communication with their provider about fracture risk, and about using bisphosphonates to reduce that risk, will improve the quality of treatment decisions. We anticipate that patients will become more involved in the decision-making process and decisions will be more consistent with patient's values and health care goals. We expect this will lead to increased bisphosphonate start and adherence in patients at high risk of fracture, and to patient's stopping medication or not starting in patients at low risk of fracture.

Normalization Process Analysis Aim: at the end of the study, we will have results concerning the efficacy of the decision aid from the trial, as well as evidence of the extent to which nurses can facilitate the normalization of the decision aid into clinical practice.

Analysis of video-taped patient-clinician encounters: as a secondary aim, we will analyze videotapes of patient-clinician encounters to identify organizational, patient, and provider characteristics that promote or inhibit uptake of the decision aid in clinical practice.

**Methods**

**Description of Recruitment Methods:**

The Olmsted Medical Center (OMC), Rochester, has been added as a site. OMC study coordinators will recruit and consent patients. Enrolled patients and clinicians who consent to having the clinical visit recorded will be video and/or audio recorded via the FLIP cameras. Participating clinicians and patients will complete surveys following each encounter. The OMC study coordinator will notify the Mayo Clinic study coordinator each time a patient has enrolled in the study and arrange for all data (surveys, case report forms) and the FLIP camera to be hand delivered to the Mayo Clinic study coordinator.

In the event that there are any modifications in consent documents, the Mayo Clinic Study Coordinator will submit modifications to the OMC IRB, and provide revisions to the OMC Study Coordinator.

The coordinating center PI ([name]) has all contact information for OMC personnel, and will communicate / ensure that OMC has the most current version of the protocol and any amendments to the protocol.

Any deviations from the protocol by OMC will be communicated to the Mayo Clinic study coordinator or PI within 3 business days.

**Data management, video and audio recordings between OMC and Mayo clinics:**

Both sites will be required to use the current version of all documents and forms. All forms, documents and video/audio recordings completed at OMC will be immediately brought to the OMC Research Office. The OMC staff will contact a Mayo, KER Unit study coordinator, who will arrange to pick up the study materials that day at the OMC Research Office. If this cannot be accomplished that day, the study materials will be placed in a locked cabinet until the Mayo study coordinator is available. The Mayo Study Coordinator will place the "Flip" camera and all study documents in a locked PHI folder (which is HIPAA compliant). The study materials will then be immediately transported to the KER Unit office, where the all study materials will be stored in a locked file cabinet. Digital recordings from the FLIP camera are uploaded to the KER Unit's secure server, and deleted from the portable devices. The video and audio files are identified using a code number that does not include the name of the clinician or patient. Transcriptions will omit patient and clinician names that may have been stated during the recording. The research data are only accessible with password protected and logged access at the KER Unit at Mayo Clinic. All Mayo personnel with access to study data have received human subjects’ research training.

**How will patients be identified?**

We will identify eligible women from lists of upcoming bone mineral density (BMD) evaluations and from participating providers' appointment calendars.

For the Normalization Process Analysis, we will identify 3 nurses who work directly with one primary care clinician, and meet with them to determine the following:

Qualitative Taxonomy of Tasks: This group of nurses will be provided with background information concerning the OSTEOPOROSIS CHOICE II decision aid study, and then consider the work that goes into the preparation of the decision aid, and a preliminary discussion with the patient of the patient’s risk factors for an osteoporotic fracture in the next 10 years. They will focus on the work of the nurse, as well as the other members of their work unit (other nurses, clinicians, clerks). Participants will build a taxonomy of tasks involved in making the intervention a part of their routine, qualitatively assess the relative importance to participants, and identify potential conflicts between new and existing tasks.

Verifiable Propositions: We will subject the above data to qualitative procedures of constant comparison (Glaser 1965) to develop a master taxonomy of tasks, subjective assessments of their relative importance, and potential conflicts between proposed and existing tasks. This master taxonomy will be used to identify factors that will promote or inhibit the operationalization of the intervention, and a set of theory-based explanations for these factors can be empirically tested.

Structured Data: The verifiable propositions will: a) be distilled as additional questions for post-visit surveys of nurse(s) (e.g., “How difficult was it for you to prepare the decision and discuss the patient’s risk factors, given the other roles and responsibilities you hold?), and b) provide a framework for a structured observation manual. Study coordinators will carry this observational manual during the study, and make notes of verbal, nonverbal and other clues that indicate difficulties faced by nurses or other unit personnel, when nurses are preparing / discussing the decision aid with a patient.

Normalization Process Analysis: After all patients have been recruited, we will meet with participating nurses to determine the work that actually went into the implementation of the decision aid prep and discussion, what work this represented to others, and other factors that may inhibit or facilitate implementation.

When a patient has consented to participate in the study, the 3 identified nurses will meet with their patient and do the following:

After the patient has met with the study coordinator and provided informed consent to participate, the clinician will meet with their patient as they usually do in the examination room. If the clinician and their patient agree to do so, their visit will be videotaped. The consent document for clinician will have the following language:

“Your patient will be randomized to one of three groups by chance. Depending on which group your patient is in, you may share information about your patient’s treatment options, including bisphosphonate therapy, using different visual aids. If you and your patient agree to do so, your visit with your patient will be videotaped. If your patient is randomized to the control arm, you will meet with your patient in the usual fashion. If your patient is randomized to the FRAX or the FRAX + decision aid arm, you will discuss their fracture risk with them. Following your visit with your patient you will be asked to answer a short survey of 3-4 questions, which should take about one minute to complete.”

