**Statistical Considerations**

**Endpoints**

**Primary:** Medication start/stop, knowledge, and patient involvement will be the primary outcome measures. Medication start / stop will be assessed at meeting with clinician and at 6 months via self-report and pharmacy records.

**Secondary:** Decisional quality (i.e. knowledge, decisional conflict) will be assessed at baseline and at 6 months via phone surveys.

Normalization Process Analysis: At the end of the study, we will have results concerning the efficacy of the decision aid from the trial, as well as evidence of the extent to which nurses can facilitate the normalization of the decision aid into clinical practice.

Secondary analysis of videotaped patient clinician encounters. Two reviewers working independently and in duplicate will review the video recordings to determine eligibility and to extract data for analyses. Videotapes of eligible encounters will be reviewed to identify characteristics of patients, clinicians and patient-clinician interactions associated with use of the decision aid in clinical practice after the trial is complete.

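### The coordinator observation rule for nurse work records only difficulties, although the analysis is meant to identify promoting as well as inhibiting factors

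*Protocol*

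**What the plan says.** The relevant text is in the Protocol under *How will patients be identified?*, in the paragraphs on the Normalization Process Analysis.

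- **Verifiable Propositions.** Nurse discussions are condensed into a master list of tasks, which is to "identify factors that will promote or inhibit the operationalization of the intervention". The explanations drawn from it are meant to be open to empirical testing.
- **Structured Data.** The propositions have two uses. They become extra questions in the nurses' post-visit surveys, illustrated by an item beginning "How difficult was it for you to prepare the decision". They also "provide a framework for a structured observation manual". Coordinators carry that manual during the study and are to "make notes of verbal, nonverbal and other clues that indicate difficulties faced by nurses or other unit personnel" while nurses prepare or discuss the decision aid.
- **Normalization Process Analysis.** Once recruitment is complete, the participating nurses are asked what work was actually involved and about "other factors that may inhibit or facilitate implementation".

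The Aims section and the Endpoints section both state what the analysis should deliver: "evidence of the extent to which nurses can facilitate the normalization of the decision aid into clinical practice".

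**The concern.** The purpose is two-sided and the recording rule is one-sided. A coordinator who follows the sentence as written notes signs of trouble and nothing else. A step that helped produces no note, and neither does a visit without difficulty.

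This matters because of timing. The coordinator's notes are the only direct observation of nurse work made while that work is being done. If helpful features are not noted then, no later analysis of the notes can recover them. A finding that few promoting factors were observed could reflect the instruction rather than practice. The notes alone would also not show how many observed visits passed without a problem, which a reader needs in order to judge how common the problems were.

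**Working it through.** No arithmetic applies. The protocol gives no figure on this point, and the question is whether a recording rule matches its purpose. The check is to take each source that bears on nurse work and ask which direction its stated wording covers and when the data arise.

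1. **Purpose (Verifiable Propositions).** Two-sided: both promoting and inhibiting factors are named.
2. **Intended result (Aims; Endpoints).** How far nurses can help the decision aid become part of practice. Evidence on this should be able to show success as well as obstacles.
3. **Observation manual (Structured Data).** Its framework is the set of two-sided propositions. The next sentence, which says how the manual is used, mentions difficulties only. Data arise in real time. The mismatch lies within a single paragraph.
4. **Nurse survey (Structured Data).** The questions are to be distilled from the same two-sided propositions. One example is given, and it is framed on difficulty. The answer format is not stated and the remaining questions are not shown. Data arise after each visit.
5. **Closing nurse meeting (Normalization Process Analysis).** Two-sided in its wording. Data arise after all patients have been recruited.
6. **Video analysis (Aims; Endpoints).** The Aims section states it as two-sided, and it works from visit recordings. Its subject is the encounter between patient and clinician, not the nurse's preparation and preliminary discussion.

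Item 3 is the only real-time source on nurse work, and its stated rule covers one direction. Item 4 may cover both, but the document does not show this and its sole example leans the same way. Item 5 covers both, in retrospect. Item 6 covers both, on a different part of the visit.

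The mismatch between items 1 and 3 is therefore established from the text. It does not follow that the analysis as a whole lacks information on promoting factors, because items 4 and 5 remain available.

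**The case against.** The strongest reply is that both structured instruments are built from propositions covering both directions, that neither instrument has yet been written, and that one sentence and one example should not be taken as the whole design. That stands for the survey: the difficulty item is explicitly an example. It does not rescue the observation rule, which is stated outright and narrows a manual that is otherwise framed broadly.

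A second reply is that a post-visit question on difficulty can be answered as not difficult, so a smooth visit can leave a record and completed surveys can supply a denominator. This is correct, subject to the unstated answer format. The gap is confined to the coordinator's notes, and low difficulty is still not evidence of what helped.

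A third reply is that the aim asks whether nurses can carry this work, and that difficulty alongside their other duties bears directly on it. This is fair, and records of difficulty belong in the data. It does not explain why visits without difficulty should go unrecorded, and the propositions themselves name promoting factors.

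Three stronger readings are tempting, and the document does not support them:

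- A reader might infer that promoting factors cannot be tested at all. The survey questions come from two-sided propositions and may well address them.
- A reader might infer that the evidence on facilitation would rest on end-of-study recall alone. That assumes the unseen survey contributes nothing.
- A reader might try to size the problem by estimating how many aid visits the three nurses would see. The protocol gives only a maximum of 100 clinicians, not an expected number, and no distribution of patients across them. A visit count would also not measure one-sided wording.

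**Conclusion.** The point holds as a specific, minor mismatch. The coordinator observation rule asks only for signs of difficulty, while the propositions that frame the manual and the aim it serves call for evidence in both directions. As written, real-time observation of nurse work leans toward barriers and leaves no note of a smooth visit. Evidence on what helped would depend on survey questions still to be written and on the meeting after recruitment.

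The conclusion assumes that coordinators apply the sentence literally and that the finished manual does not widen it. If the manual already has space for helpful features and for visits without difficulty, only the protocol sentence needs correcting. The Schematic Design section describes this addendum as a qualitative assessment. Nothing here affects the randomized comparison, the trial's primary outcomes, the sample size or the power.

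**What to change.** In the Structured Data paragraph, amend the sentence on coordinator notes so that the observation form is completed at each observed decision-aid visit of a participating nurse. It should record clues to what helped as well as what hindered, with an explicit entry for no difficulty. Reword the sample survey item neutrally, for example *How easy or difficult was it…*.

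The change should be made before observation begins, because unrecorded observations cannot be reconstructed. It needs no new staff or visits. The cost is a wording change in the protocol and manual, one reworded survey item, and slightly more form-filling for coordinators, who would also complete a form when nothing went wrong.
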